#### 11.1.5 Secondary Endpoints

SSI will be the first secondary endpoint. Mean changes from baseline will be analyzed using a restricted maximum likelihood (REML)-based repeated measures approach. Analyses will include the fixed, categorical effects of treatment, investigative site, visit, and treatment-by-visit interaction, as well as the continuous, fixed covariates of baseline score and baseline score-by-visit-interaction. Although we will provide training to minimize differences in site, it is recommended the investigative site be included in models of clinical trial data to account for any chance that site-specific subjectivity may influence outcomes (Ting, 2018). A treatment-by-visit interaction allows the effects of the treatment to differ by visit (Ting, 2018). It is reasonable to model the possibility that treatment effects differ by visit because each “dose” of treatment includes different content, study follow-up occurs after treatment has ended, and the study follow-up occurs over an extended period of time. The score-by-visit interaction accounts for the possibility that the impact of baseline to responses at different visits could be different (Ting, 2018). An unstructured (co)variance structure will be used to model the within-subject errors. The Kenward-Roger approximation will be used to estimate denominator degrees of freedom and adjust standard errors. Significance tests will be based on differences of least-squares means using a two-sided  $\alpha=0.05$  (two-sided 95% confidence intervals). Analyses will be implemented using SAS Version 9.4. For SSI, the primary treatment comparison will be the contrast between treatments at 24 weeks. Exploratory models will examine SSI at study end. The same model will be applied for exploratory testing intervention effects on the BDI-II and BHS at study end.

The hypothesized mediators are impulsive decision-making and emotion regulation. In the mediation model, treatment condition will be the independent variable and, SAs (defined as a binary variable) will be the outcome variable. We will use regression parameters and their standard errors with 10,000 bootstrapped resamples as recommended by Preacher et al. (2004) to test for mediation. Mathematically, the mediation path will be defined as the product of coefficients for the path from the independent variable to the mediator (path a) and the path from the mediator to outcome variable (path b). Thus, we will test the statistical significance of  $a*b$ .

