### 7.5 RANDOMIZATION CRITERIA

Participants who meet the eligibility criteria will be assigned a participant number and will then be randomly assigned to the Aviva + TAU or sham + TAU groups. A computerized modified minimization randomization procedure within the electronic Case Report Forms (eCRFs) will be used. Eligible participants will be randomized based on study site, sex, race/ethnicity and whether they have had no attempts, single attempts or multiple suicide attempts. This adaptive randomization method has been shown to be superior to stratified randomization in producing balance for separate prognostic variables, particularly when the number of strata is large compared with the number of subjects. Once the participant is randomized the site staff will make sure that the participant has properly loaded Aviva **or** sham app onto his/her phone. The PI or designee will confirm that the app has been downloaded and, if the participant is having difficulty, assist them beginning the onboarding session.

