The sensitivity analyses will proceed in the following manner: the primary analysis will be repeated in the per-protocol population and the Cox proportional hazards model will be carried out on the ITT population to investigate the robustness of the finding for suicide attempt in the presence of potentially important factors such as sex, race/ethnicity, and site. The ITT will be used for the primary and secondary endpoint analysis either here or in the sections above where each is discussed. Associated Wald tests will be conducted using a significance level of .05 (2-sided) to test the null hypothesis that the two time-to-event distributions are the same for the Aviva and sham groups at any time point. We will conduct subgroup analysis based on the stratification factors used in our randomization (sex, race/ethnicity and previous suicide attempt history [i.e., whether participants had no suicide attempts, a single attempt or multiple suicide attempts] and investigative site). We will include sex, race/ethnicity because differences in rates (or increases in rates) have been observed for each. Regarding sex, the age adjusted suicide death rate for males (22.79 per 100,000) is higher than the rate for females (6.18 per 100,000; CDC, 2020). For race/ethnicity, American Indian/Alaska Native adults are at highest risk for past-year suicide attempts, followed by Black and Hispanic adults (CDC, 2020). Lastly, while all efforts will be made to standardize procedures across sites, it is possible that site differences may emerge. Thus, we will examine whether there are any treatment differences based on sites. Lastly, previous suicide attempt history is a strong predictor of future suicide attempts.

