#### 12.2 *REDUCE LIKELIHOOD OF SELECTION BIAS IN RECRUITMENT AND ENROLLMENT*

- Recruitment: There will be training sessions that explain the inclusion/exclusion criteria and importance of the study and randomization to the staff.
- Enrollment in treatment arms: As previously noted, we will reduce selection bias by using a randomization procedure that adjusts for factors that may affect outcomes. Our randomization will occur with allocation concealment.

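### The suicidal-ideation model adjusts for only one of the four factors used in minimisation (site); adding sex, race/ethnicity and attempt history would cost little and remove a possible small overstatement of its standard error

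*Protocol*

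**What the plan says.** Protocol section 7.5 sets the allocation method: "A computerized modified minimization randomization procedure within the electronic Case Report Forms (eCRFs) will be used". Participants are "randomized based on study site, sex, race/ethnicity and whether they have had no attempts, single attempts or multiple suicide attempts". Section 12.2 describes this as "using a randomization procedure that adjusts for factors that may affect outcomes".

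Section 11.1.5 then fixes the SSI model term by term: "Analyses will include the fixed, categorical effects of treatment, investigative site, visit, and treatment-by-visit interaction". The SSI value at baseline, and its interaction with visit, enter as continuous terms. The section also sets an unstructured covariance, Kenward-Roger degrees of freedom, the 24-week contrast and a two-sided 0.05 level. The same model serves the Beck Depression Inventory (BDI-II) and the Beck Hopelessness Scale (BHS). It gives a reason for including site and does not mention the other three balancing factors.

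No other section adjusts SSI for them. Section 11.3 puts sex, race/ethnicity and site into a sensitivity Cox model for suicide attempts and uses the randomisation factors for subgroup analyses. Section 11.4 mentions only centre as a nuisance factor.

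**The concern.** Minimisation reduces chance imbalance between the arms in the factors it uses. If those factors predict the outcome, the treatment difference varies less from one hypothetical trial to the next than it would under simple randomisation. A model that omits them still counts their variance as residual error, so its reported standard error does not reflect that reduction. The interval is then wider than it should be and the test conservative.

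SSI at 24 weeks is the first secondary endpoint and is tested at 0.05 once the primary endpoint succeeds (section 3.2.1), so its interval and p-value carry weight. Because section 11.1.5 fixes the terms, an analysis plan that followed it would inherit the omission, and one that added the factors would depart from the protocol.

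**Working it through.** **The plan's own figure.** Attachment D assumes a difference of 3.8, SD 7.6 and two-sided alpha 0.05. A noncentral-t calculation for two equal arms reproduces it exactly: 0.83582, 0.88160, 0.91559 and 0.94043 at 70, 80, 90 and 100 per arm. With the 195 and 196 participants of section 11.1.4 the same formula gives 0.9985. With 20% missing (0.8 × 195 = 156 per arm) it gives 0.993.

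**Perfect-balance limit.** Let R² be the share of week-24 SSI variance, after baseline SSI and site, that the three omitted factors explain. The protocol does not give R², so a range is assumed. If balance on the factors is perfect, the ratio of reported to true standard error is 1/√(1 − R²), and the true two-sided type I error is 2[1 − Φ(1.96/√(1 − R²))].

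| Assumed R² | Reported / true SE | True type I error |
|---|---|---|
| 0.02 | 1.010 | 0.048 |
| 0.05 | 1.026 | 0.044 |
| 0.10 | 1.054 | 0.039 |
| 0.20 | 1.118 | 0.028 |

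**Imperfect balance.** Real minimisation with a random element balances less tightly, so the limit was checked by simulation with 4,000 trials per setting. Each trial had 391 participants, 20% of outcomes missing at random, and minimisation on all four factors with a biased coin of 0.8. Further assumptions were six equal sites, sex 50:50, race/ethnicity in four groups (60, 17, 15 and 8%) and attempt history 35, 30 and 35%. A single-visit analysis of covariance stood in for the week-24 contrast. Type I error is in brackets.

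| Assumed R² | Reported / true SE, factors omitted | Reported / true SE, factors included |
|---|---|---|
| 0 | 0.996 (0.055) | 0.996 (0.053) |
| 0.05 | 1.006 (0.050) | 0.986 (0.055) |
| 0.10 | 1.031 (0.041) | 0.995 (0.049) |
| 0.20 | 1.081 (0.034) | 0.988 (0.051) |

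Monte Carlo error is about 1/√(2 × 4000) = 1.1% on each ratio and √(0.05 × 0.95/4000) = 0.003 on each type I error. The 1.006 therefore cannot be told apart from 1, while 1.031 and 1.081 can. Under simple randomisation at R² 0.20, omitting the factors gave 0.975 (0.055), so the overstatement comes from combining minimisation with an unadjusted model.

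**Two separate quantities.** The limit formula also describes how much the reported standard error falls on adjustment. At R² 0.10 the mean reported value went from 0.1135 to 0.1079, a ratio of 1.052. Of that, about 3% is the overstatement above. Part of the rest is a real gain in precision: the true standard deviation of the estimate fell from 0.1101 to 0.1085, a ratio of 1.015.

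**Effect on power.** Take 156 per arm and SE = 7.6 × √(2/156) = 0.86. With the factors omitted, power in the perfect-balance limit is 1 − Φ[(1.96 − δ/SE)/√(1 − R²)]. With them included it is the noncentral-t power with SD 7.6 × √(1 − R²). At R² 0.10 and δ = 3.8 the two are 0.995 and 0.996. At an assumed δ of 2.0 they are 0.65 and 0.69, and at R² 0.20 they are 0.66 and 0.74.

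**The case against.** A reader might infer that the SSI standard errors are simply too large. The documents do not support that as a fact. It holds only if the three factors predict week-24 SSI beyond baseline SSI and site, and no section says they do. Section 11.3 states that "previous suicide attempt history is a strong predictor of future suicide attempts", which concerns attempts and not ideation. Its remarks on sex and race/ethnicity likewise concern suicide deaths and attempts, and section 12.2 says only that the factors may affect outcomes. At R² = 0 the two models agree.

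The size is also uncertain. Section 7.5 gives neither the assignment probability nor the weights, so how tightly the factors are balanced is unknown. The formula values are an upper limit for a given R².

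A third point is that main effects alone may not remove the factors' week-24 variance if their influence changes over time. That stands, and the fix allows for it. The check used one visit and not the full repeated-measures model.

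Finally, nothing in section 11.1.5 is misstated, and the planned conclusion is practically unaffected. That also stands and is why the point ranks low. The reason to raise it is that the model is fixed in the protocol and the change is nearly free.

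**Conclusion.** The mismatch between sections 7.5 and 11.1.5 is plain: one of four balancing factors enters the SSI model. Its consequence is conditional and small. For an assumed R² of 0.05 to 0.10 the reported standard error would be about 1% to 3% too large with a 0.8 biased coin, and at most 2.6% to 5.4% under perfect balance. It would not be overstated at all if the factors are not prognostic for SSI.

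Any error is on the conservative side, and power at the planned difference stays above 99%. The benefit shows mainly if the true difference is well below 3.8. This is an inexpensive improvement in precision and calibration, and it does not threaten the trial's conclusion. The figures rest on the assumed R², factor frequencies, number of sites and coin probability.

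**What to change.** In section 11.1.5, add sex, race/ethnicity and attempt history (none, single, multiple) to the SSI model as fixed categorical effects. Add their interactions with visit where the effects may differ by visit, as is already done for baseline score. Combine sparse race/ethnicity levels by a rule set before unblinding, since section 7.5 does not define the levels. Use the same model for BDI-II and BHS.

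The factors are already recorded at randomisation, so no data collection changes. With four race/ethnicity groups (assumed), the cost is 1 + 3 + 2 = 6 degrees of freedom out of about 390. With full by-visit terms it is about six coefficients at each visit.

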| Secondary Objectives   | To evaluate the effectiveness of Aviva + TAU (vs. a sham app + TAU) on suicide ideation (at 24 weeks).

To explore whether changes in decision-making and emotion regulation are mechanisms of action for Aviva.                                                                                                                                                                                                                                                                                                                                                                                                                                                                                |
| Safety Objectives      | To evaluate the safety of Aviva + TAU (vs. a sham app + TAU).                                                                                                                                                                                                                                                                                                                                                                                                                                                                                                                                                                                                                                         |
| Number of Participants | 391                                                                                                                                                                                                                                                                                                                                                                                                                                                                                                                                                                                                                                                                                                   |

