## **3. OBJECTIVES AND HYPOTHESES**

### **3.1 PRIMARY OBJECTIVES AND HYPOTHESES**

The primary objective of this study is to assess the effectiveness of a digital intervention (Aviva) in reducing suicide attempts in patients with a recent history of suicidal ideation or attempted suicide. The time to first suicide attempt after randomization is the primary endpoint. Time to event analysis will occur when the expected number of events occur.

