#### **3.2.2 Additional Secondary Objectives**

Since cognitive behavioral therapy for suicide prevention (CBT-SP) is hypothesized to target decision-making and self-regulation processes, OUI will use bias-corrected bootstrapped estimates to conduct exploratory analyses (specifically mediation analyses; Preacher and Hayes, 2014) examining Aviva's effects on SA and SI through participants' scores on the Monetary Choice Questionnaire (MCQ) and the Cognitive Emotion Regulation Questionnaire (CERQ), respectively. Exploratory analyses will assess treatment effect trends by obtaining additional assessments of suicide ideation, depression, and hopelessness from weeks 0 to 104. Depression will be assessed using the BDI-II (Beck, Steer & Brown, 1996). Analyses will examine change in total score on the BDI-II. Hopelessness will be assessed using the BHS (Beck & Steer, 1988; Beck, Weissman, Lester, & Trexler, 1974).

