## 7. STUDY ASSESSMENTS AND PROCEDURES

### 7.1 ASSESSMENTS

The assessments for this study are shown in Table 1. Baseline assessments are done in person at the Screening or Baseline visit. All assessments after Day 0 will be administered over the phone with site staff. These assessments are consistent with the set of assessments used by other studies (Rudd, et al. 2015; Brown, et al. 2005). All assessors will be blinded to participant treatment assignment. Additional details as follows.

| Assessment                                    | Construct        | Description                                                                                                                                                                                                                                                                                                                                                                   | Study Week (W)                              |
|-----------------------------------------------|------------------|-------------------------------------------------------------------------------------------------------------------------------------------------------------------------------------------------------------------------------------------------------------------------------------------------------------------------------------------------------------------------------|---------------------------------------------|
| Primary Effectiveness Outcome          |                  |                                                                                                                                                                                                                                                                                                                                                                               |                                             |
| Suicide Attempt Self-Injury Interview (SASII) | Suicide attempts | Two methods will be used to assess suicide attempts: a) SASII and b) medical record review. The incidence of suicide-related behavior (actual, interrupted, aborted, preparatory behaviors) is of interest, but actual attempts is the primary effectiveness outcome. If either the SASII clinical interview or the medical record review indicates a suicide attempt, | Screening, W4, W8, W12, W24, W52, W78, W104 |

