| Clinical Global Impression change subscale (CGI-C)   | Clinical improvement      | Clinical improvement will also be assessed with the Clinical Global Impression change subscale (CGI-C). It assesses how much the participant's illness has improved or worsened relative to their baseline state at the beginning of the intervention on a scale ranging from 1 (very much improved) to 8 (very much worse).                                                                                                                                                                            | W12, W24, W52, W78, W104                   |
| Mechanisms of Action                          |                           |                                                                                                                                                                                                                                                                                                                                                                                                                                                                                                         |                                            |
| Monetary Choice Questionnaire (MCQ)                  | Impulsive decision making | Impulsive decision making will be assessed using the Monetary Choice Questionnaire (MCQ), a self-report questionnaire that presents a series of 27 monetary choices, each of which includes a smaller, immediate monetary reward and a larger, delayed monetary reward (Kirby et al., 2019). Higher values indicate a preference for immediate rewards and impulsivity. MCQ is temporally stable and has been shown to be associated with suicidal behaviors (Dombrovski et al., 2011, 2012).           | Baseline, W12, W24, W52, W78               |
| Cognitive Emotion Regulation Questionnaire (CERQ)    | Emotion regulation        | Emotion regulation will be assessed using the Cognitive Emotion Regulation Questionnaire (CERQ) self-report questionnaire that assesses a range of psychological strategies used in response to emotionally threatening or stressful events (e.g., self-blame, rumination, positive reappraisal). The CERQ is a reliable and valid measure of emotion regulation, and its subscales correlate with emotional distress and psychopathology in the expected directions (Garnefski, N., Kraaij, V., 2007). | Baseline, W12, W24, W52, W78               |

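### The exploratory mediation model lets suicide attempts count as outcomes of a mediator that is measured only after them

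*Protocol*

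**What the plan says.** The Synopsis lists among the secondary objectives: "To explore whether changes in decision-making and emotion regulation are mechanisms of action for Aviva". Section 3.2.2 calls the mediation analyses exploratory. It names attempts (SA) and ideation (SI) as outcomes, acting through "scores on the Monetary Choice Questionnaire (MCQ) and the Cognitive Emotion Regulation Questionnaire (CERQ), respectively", with bias-corrected bootstrap estimates.

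Section 11.1.5 gives the model: "treatment condition will be the independent variable and, SAs (defined as a binary variable) will be the outcome variable". The indirect effect is the product of path a (treatment to mediator) and path b (mediator to outcome), with 10,000 bootstrap resamples: "Thus, we will test the statistical significance of" a*b. The section does not say which visit supplies the mediator or from when attempts count, and it sets out no model for SI.

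The schedule for MCQ and CERQ in Section 7.1 and Table 1 is "Baseline, W12, W24, W52, W78". Attempts are assessed with the SASII at "Screening, W4, W8, W12, W24, W52, W78, W104". For the primary endpoint they count from randomization (Section 3.1): "The time to first suicide attempt after randomization is the primary endpoint".

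**The concern.** A mediator has to come before the outcome it is said to explain. Nothing is measured on MCQ or CERQ between baseline and week 12, yet attempts are recorded from week 4, and the binary outcome in 11.1.5 is not restricted to later ones. A participant who attempts in week 3 would enter path b with a score taken nine weeks afterwards. An attempt may itself worsen emotion regulation or decision-making. Path b would then pick up an association that runs from attempt to score, while path a is a genuine treatment effect on the score. Their product can reach significance with no mediation at all. A participant who dies before week 12 has no post-baseline mediator value.

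At stake is the reading of a positive a*b as evidence on how Aviva works. No success criterion of the trial depends on it.

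**Working it through.** **Inputs (Attachment C; Sections 11.1.3 and 11.1.4).** 195 sham and 196 Aviva participants; exponential hazards 0.0115 and 0.0115 × 0.3826 = 0.0044 per month; uniform accrual over 12 months; 24 months in total; no loss of attempt data; drift 3.4387; 52 events.

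**Reproducing the plan's figures.** Event probability per arm = 1 − [exp(−12λ) − exp(−24λ)]/(12λ).
- Sham: 0.1863 × 195 = 36.3. Aviva: 0.0760 × 196 = 14.9. Total 51.2; each arm rounded up gives 37 + 15 = 52, as stated.
- Events from the drift: 4 × 3.4387² / ln(0.3826)² = 51.24. Divided by the mean event probability of 0.1312 this gives N = 390.6, stated as 391.

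**Attempts before the mediator.** With m = weeks × 24/104 months, attempts before m = 195(1 − exp(−0.0115m)) + 196(1 − exp(−0.0044m)).
- Week 12 (m = 2.77): 6.1 + 2.4 = 8.5, i.e. 8.5/52 = 16%. The share is similar in both arms (17% sham, 16% Aviva).
- Week 24 (m = 5.54): 12.0 + 4.7 = 16.8 (unrounded sum), i.e. 32% of 52.
- Week 52 (m = 12): 25.1 + 10.1 = 35.2, i.e. 69% of 51.2.
- If everyone is followed for 24 months, 66.7 attempts are expected and the week-12 share is 8.5/66.7 = 13%.
- Attempts left after week 12: 51.2 − 8.5 = 42.7.

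A front-loaded hazard is an assumption; the protocol models a constant one. Weibull shapes 0.8, 0.6, 0.5 and 0.4 with the same 18-month sham survival put 24%, 35%, 41% and 50% of attempts before week 12.

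**Effect on the a*b test.** The simulation assumptions are not in the protocol: Aviva shifts the mediator by 0.4 SD, the mediator has no effect on attempts, and an attempt before week 12 worsens the week-12 score by the amount shown. The test level is taken as 5%. The ranges span three runs of 150, 300 and 400 trials per setting (300 to 400 resamples each), using a percentile bootstrap.

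| Hazard | Worsening after early attempt | False significance, all attempts counted |
|---|---|---|
| Constant | 0.5 SD | 9-14% |
| Constant | 1.0 SD | 18-21% |
| Doubled to week 12 | 0.5 SD | 19% |
| Doubled to week 12 | 1.0 SD | 46-54% |

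- Counting only attempts after week 12 among those attempt-free gave 3-9% over all settings, mostly near 5%.
- With no effect of attempts on the score, the test on all attempts gave 7% in the 400-trial run. Most of the excess in the table is therefore reverse causation.
- The bias-corrected bootstrap named in 3.2.2 ran higher in the 400-trial run: 15%, 26%, 23% and 53% for the four rows, 9-10% with no reverse effect, and 7-8% with later attempts only.

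These figures measure what restricting the outcome window does. They do not measure what a time-to-event model adds.

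**The case against.** The strongest reply is that 11.1.5 only outlines an exploratory analysis. Mediator visit and outcome window are details that a statistical analysis plan, not shown here, would normally fix. The section does not itself say that attempts count from randomization; that is inferred from the primary endpoint. This stands in part, and it is why severity is low. But the section does fix the outcome, the paths, the resampling and the test, and followed as written it admits attempts that precede the mediator.

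The inflation also rests on assumed effect sizes, and at the mild end it is modest. With 150 trials, 14% has a 95% interval of about 9-20%, and the highest landmark figure, 9%, about 5-15%; these overlap. The direction is consistent across runs, but the exact size is not established.

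Several stronger inferences are tempting, and the documents do not support them:
- *The mechanism objective cannot be answered, because many attempts come too early.* About 43 attempts follow week 12 on the protocol's hazards, and data already scheduled allow an ordered analysis. The ideation path is in order if week-12 scores predict week-24 SSI.
- *The protocol identifies the early weeks as the high-risk period.* Section 11.1.2 has only a bracketed remark about risk soon after discharge, in an argument for early stopping, with no hazard figure.
- *The share of misordered attempts is far higher at the first look, and a binary outcome ignores follow-up of 12 to 24 months.* Both suppose that the mediation analysis is run at an event-driven cut. Its timing is not fixed: the Synopsis expects 104 weeks of follow-up, and Section 9.9 keeps study staff and sponsor blinded until all participants have completed it, unless the DSMB stops the study.

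**Conclusion.** The point holds in a limited form. As written, the attempt mediation model counts attempts that occurred before the mediator was measured. With a week-12 mediator this is about 8.5 of 52 expected attempts (16%) under the protocol's constant hazards. It is about a third with a week-24 mediator, and more if risk is front-loaded, which is an assumption. If an early attempt worsens the score by an assumed 0.5-1.0 SD, false significance of a*b is roughly 10-20% at constant hazard, against about 5-7% when only later attempts count. Figures near 50% need the larger worsening and a doubled early hazard together.

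Separately, 3.2.2 promises an ideation outcome that 11.1.5 does not model. A reader might infer that the trial's effectiveness conclusion is at risk. It is not: the log-rank analysis does not use the mediators. Severity is low.

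**What to change.** In 11.1.5:
- Name the mediator as the week-12 MCQ or CERQ score, adjusted for its baseline value.
- Define the attempt outcome as time from week 12 to first attempt among participants attempt-free at the week-12 assessment. Use a Cox or discrete-time model for path b and keep the bootstrap. This also handles unequal follow-up, should the analysis be run early.
- Add SSI at week 24 as the ideation outcome of the week-12 mediator, as 3.2.2 promises.
- State that attempts before week 12 do not enter the attempt mediation model.

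No new visit, instrument or participant is needed. The wording should be settled before unblinding, so that the window is not chosen after results are seen.

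The limits should be stated with it. The model drops about 8-9 events and cannot speak to mechanism during the 12-week app period. It also conditions on being attempt-free at week 12, a selection that treatment can affect. On the protocol's hazards the exclusions are 6.1/195 = 3.1% in sham and 2.4/196 = 1.2% in Aviva, so the selection is small unless early risk is higher. The landmark is one defensible choice; the essential change is that only attempts after the mediator visit count.

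### The exploratory mediation test names no baseline MCQ or CERQ score, so a follow-up score that only marks prior risk can pass for a mechanism

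*Protocol*

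**What the plan says.** The Synopsis lists among the secondary objectives: "To explore whether changes in decision-making and emotion regulation are mechanisms of action for Aviva". Section 3.2.2 gives the status and method: "OUI will use bias-corrected bootstrapped estimates to conduct exploratory analyses".

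Section 11.1.5 then sets out the model. Treatment is the independent variable, impulsive decision-making (MCQ) and emotion regulation (CERQ) are the mediators, and "SAs (defined as a binary variable) will be the outcome variable". The test uses "regression parameters and their standard errors with 10,000 bootstrapped resamples". The mediation path is the product of the coefficients for "the path from the independent variable to the mediator (path a) and the path from the mediator to outcome variable (path b"), and the significance of that product is what is tested. No covariate is named as included or excluded, and it is not said whether treatment stays in the path b regression.

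The paragraph just before it, on SSI, does list its covariates, among them site and, in its words, "as well as the continuous, fixed covariates of baseline score and baseline score-by-visit-interaction". The assessment table in section 7.1 schedules both MCQ and CERQ at "Baseline, W12, W24, W52, W78", so a baseline value exists. The same table says of MCQ: "MCQ is temporally stable and has been shown to be associated with suicidal behaviors".

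**The concern.** Nobody is randomized to a value of the mediator. Treatment is balanced against prior risk, so path a is protected; the follow-up MCQ or CERQ score is not, so path b is open to confounding. If a score is stable within a person and people with worse scores were already more likely to attempt, the follow-up score predicts attempts even when the change produced by Aviva does nothing. Path b is then non-zero. Once Aviva also moves the score, a*b can be significant.

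The stated question is whether changes in these processes are the mechanism. Without the baseline score, the test can instead answer whether Aviva moves the score and the score marks risk. The trial could then report decision-making as Aviva's mechanism when MCQ is only a marker of risk that predates treatment.

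**Working it through.** **Inputs from the protocol.** N = 391 (196 Aviva, 195 sham), 52 events, HR 0.3826, one-sided alpha 0.025, 90% power, 18-month survival 0.9240 (Aviva) and 0.8124 (sham), 24 months in total with 12 months of accrual (11.1.3, 11.1.4); drift 3.4387 (Attachment C). The protocol gives no figure for the mediation test, so N and the event count fix its scale.

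**Reproducing N and events.**
- Fixed-design events (Schoenfeld): 4 × (1.960 + 1.2816)² / (ln 0.3826)² = 42.03 / 0.923 = 45.5.
- Group sequential inflation: (3.4387 / 3.2415)² = 1.125. Events: 45.5 × 1.125 = 51.2, against 52 stated.
- Hazards: −ln(0.8124)/18 = 0.01154 (sham) and −ln(0.9240)/18 = 0.00439 (Aviva).
- Event probability with uniform accrual: 1 − (e^(−12λ) − e^(−24λ)) / (12λ) = 0.187 (sham) and 0.076 (Aviva).
- Expected events: 195 × 0.187 + 196 × 0.076 = 36.5 + 14.9, or 51.3 before rounding. N = 2 × 51.24 / (0.18695 + 0.07589) = 390, against 391 stated.

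Both figures reproduce.

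**Simulating the mediation test under no mediation.** Baseline score t is standard normal. The follow-up score is M = ρt + shift × treatment + √(1 − ρ²) × noise. The log-odds of an attempt are an arm-specific constant plus ln(OR) × t; the constants match the event probabilities above, and M has no effect. Path a is linear and path b logistic. Mediation is declared when a and b are both significant at two-sided 0.05 (800 runs per setting). ρ, OR and shift are assumptions, since the protocol gives none of them.

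Rate of false mediation at ρ = 0.7:

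| OR per SD of baseline | Shift (SD) | Path b: mediator only | Path b: plus treatment | Treatment in b, baseline in both paths |
|---|---|---|---|---|
| 1.0 | 0.3 | 7.9% | 4.8% | 4.4% |
| 1.0 | 0.5 | 10.4% | 5.5% | 4.4% |
| 1.5 | 0.3 | 55.0% | 37.6% | 4.0% |
| 1.5 | 0.5 | 68.9% | 41.9% | 5.1% |
| 2.0 | 0.3 | 77.5% | 70.8% | 4.6% |
| 2.0 | 0.5 | 95.5% | 85.6% | 4.5% |

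Over a wider range (ρ 0.5 to 0.85, OR 1.3 to 2.0, shift 0.2 to 0.5 SD), the rate is 7% to 96% with treatment in path b and 2.5% to 5.8% once baseline is added. With OR 1.0 over the same ρ and shifts, the treatment-adjusted rate is 1% to 6%.

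**Using the bias-corrected bootstrap that the protocol names.**
- Same data model, 150 runs, 400 resamples, treatment in path b: OR 1.5 and shift 0.3 give 44% without baseline and 7% with it; OR 2 and shift 0.5 give 87% and 10%. The standard error of the 10% is √(0.10 × 0.90 / 150) = 2.4 points.
- A separate simulation (200 trials, 300 resamples, about 52 to 59 attempts, correlation 0.7): 46%, 53%, 81% and 88% without baseline, and 5%, 8%, 6% and 7% with it, for OR/shift of 1.5/0.3, 1.5/0.5, 2/0.3 and 2/0.5.

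**Limit of the remedy.** If baseline measures the underlying trait with error (shared latent trait, shift 0.5), adjustment lowers the rate from 60% to 10% at OR 1.5, but only from 98% to 39% at OR 2.

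**The case against.** The strongest reply is that section 11.1.5 is silent, not wrong. It does not call path b unadjusted or rule out the baseline score, and covariates of an exploratory model are often left to the SAP, which is not at hand. A reader might infer that the plan has decided to ignore baseline MCQ and CERQ; the text does not support that. What remains is that 11.1.5 writes out the model, the statistic and the test without a baseline score, directly after a paragraph that lists covariates for SSI. The safe specification should stand in the same place.

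The form of the mediator is also open: the Synopsis speaks of changes, section 3.2.2 of scores. If change from baseline were used, false mediation in the direction of benefit would almost vanish. The test would still reject in about 16% to 37% of null trials at the table's OR 1.5 to 2 settings, nearly all in the opposite direction, because participants with high baseline scores tend to regress and also carry more risk. Neither reading does as well as including the baseline score.

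The scenario is assumed as well. If the current trait drives attempts, a significant a*b is genuine mediation. That is the alternative hypothesis, however, and the question here is how the test behaves under the null.

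Two other stronger readings fail. A reader might infer that the test declares a mechanism whenever Aviva moves the score; the rate depends on stability, risk link and shift, and is near nominal when baseline does not mark risk. A reader might also extend the point equally to CERQ, but section 7.1 says of CERQ only that it is reliable, valid and correlated with distress and psychopathology.

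**Conclusion.** The concern holds as a minor point. As written, the exploratory mediation model has no baseline mediator score, and the protocol's own description of MCQ makes confounding of path b plausible. With correlation 0.7, OR 1.5 to 2 per SD and a shift of 0.3 to 0.5 SD, false mediation runs at roughly 35% to 90% without baseline, even with treatment in path b. With baseline it is about 3% to 8%, apart from the 10% in one short bootstrap check. These rates rest on assumed inputs and on the mediator being the follow-up score. The analysis is exploratory, and trial success rests on the time-to-attempt endpoint alone.

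**What to change.** In section 11.1.5, state that the path b regression includes treatment and that both regressions include the baseline value of the same mediator (baseline MCQ for MCQ, baseline CERQ for CERQ). Add that a significant a*b will be described as consistent with a mechanism and not as proof of one, because other mediator-outcome confounding and error in the baseline measurement can remain.

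The cost is a sentence or two and one more term per model. No new data are needed, as both baseline scores are already scheduled. Path b would then hold three terms (treatment, mediator, baseline mediator) for about 52 events, or 52 / 3 ≈ 17 events per term. I would not also require baseline SSI and attempt history: that larger model was not examined and would spread the same events more thinly.
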